### Management strategies

Clinics will be allowed to restrict notification of alerts to business hours, but will be encouraged to check the CareLink website at least once daily for transmissions.

If the clinic is notified of an audible alert sounding (both arms) or an alert received via CareLink (remote arm only), or if subjects report signs or symptoms, the clinician is required to implement management strategies that exploit the respective features available in the two arms. A summary of management strategy requirements is listed in Figure 2 for the standard arm, and in Figure 3 and 4 for the remote arm.

**Figure 2 F2:**
[figure not shown]
**Management strategy requirements**. Operative flowcharts for the management of device shocks and alerts in the standard arm.

**Figure 3 F3:**
[figure not shown]
**Management strategy requirements**. Operative flowcharts for the management of system performance alerts, device shocks and OptiVol alerts in the remote arm.

**Figure 4 F4:**
[figure not shown]
**Management strategy requirements**. Operative flowcharts for the management of atrial fibrillation alerts in the remote arm.

Assessment of the patient's clinical status and verification of appropriate functioning of the ICD will be performed in accordance with the current guidelines and the center's routine practice.

### Statistical methods

An intention-to-treat analysis will be performed on all randomized subjects and will serve as the primary analysis for all objectives in this study.

The primary and secondary hypotheses will be tested by using the Comparison of Incidence Rates (Large Sample) Test. A two-sided test and a significance level of α = 0.05 will be used.

Cost analysis will be carried out from the perspectives of the healthcare system and the patient. Consequently, the unit costs considered will be related to the public tariffs or to the patient's out-of-pocket expenses. The in-hospital resources related to the introduction and utilization of CareLink will also be evaluated.

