### Objectives

The primary objective of the study is to determine whether patients using the CareLink system display a different rate of unplanned cardiac or device-related in-hospital visits from patients in the standard arm. The endpoints for this objective include all cardiac and device-related clinic visits, i.e. all hospital admissions not involving an overnight stay, when the interval between the decision to admit and the admission is <24 hours. The events anticipated to prompt these visits are: ICD alerts regarding system integrity, atrial and ventricular arrhythmias, decrease in intra-thoracic impedance signifying possible fluid accumulation, and patients' symptoms. These endpoints will be subdivided according to whether the visits are related or not related to episodes of worsening of HF; estimation of their respective rates will constitute a secondary objective of the study.

Additionally, the rate and related costs of total healthcare utilizations (all planned and unplanned hospital admissions involving and not involving an overnight stay) for cardiac or device-related events will be compared between groups. For this objective, hospital visits will be also scrutinized and classified as necessary or unnecessary for the clinical management of the patient. In particular, each visit will be judged necessary if it results from an appropriate and clinically meaningful ICD alert (e.g.: intra-thoracic impedance alert associated with clinically deteriorated HF) and if the clinician was not previously aware of the clinical/ICD condition.

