***VF Detection/Therapy Off***		

*Alert Enable – Device*	On-High	On-High

*Alert Enable – Monitor*	On	Off

* For systems with an LV lead; ** For systems with dual-coil leads

In summary, all alerts regarding clinical management (intra-thoracic impedance for fluid accumulation monitoring, atrial arrhythmias, ICD shocks delivered) will be turned on for wireless notification through the CareLink in the remote arm, while no audible alerts will be used. In the standard arm these alerts will be turned on for audible notification only.

All lead and device integrity alerts will be turned on for both wireless and audible notification in the remote arm, and for only audible notification in the standard arm.

In the standard arm, audible alerts for intra-thoracic impedance monitoring will be programmed to sound at a different time of the day from alerts for other causes, in order to distinguish them.

Clinicians are allowed to turn off the alert for atrial arrhythmias, if they are no longer attempting to control the subject's atrial rhythm. Similarly, they can turn off the alert for intra-thoracic impedance when recurrent inappropriate detections of fluid accumulation are documented.

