### Sample size justification

The sample size requirements for this study are intended to provide adequate power for the analysis of the primary objective.

Simulation methods used data extrapolated from a population of 160 CRT-D patients followed up for 224 ± 130 days (data on file). Overall, 220 episodes occurred over 98 person-years (2.2 per person-year):

• 140 intra-thoracic impedance alerts;

• 34 episodes of atrial arrhythmia >12 hours in a single day;

• 6 additional episodes of atrial arrhythmia >6 hours with ventricular rate >100 beats/min in a single day;

• 40 ICD shocks delivered.

The simulations were run in R Software 2.4.1 according to the following hypotheses: the incidence density used as a null hypothesis was 2.2 per person-year; this rate is expected to decrease by 10% in the study arm; it was assumed that 20% of patients would drop out uniformly over the follow-up period; the target type-I error (α) was 0.05.

A sample size of 100 subjects per group would allow a power of 99.8% (95% confidence interval: 96.0 – 100.0) to detect an incidence rate ratio of 0.90, with a type-I error of 0.05.

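### The named incidence-rate test assumes independent Poisson visits, so its type I error exceeds 5% if patients' visit rates differ, by an amount the article's figures cannot fix

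*Protocol article*

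**What the plan says.** Statistical methods fixes a single test for the primary and secondary rates: "The primary and secondary hypotheses will be tested by using the Comparison of Incidence Rates (Large Sample) Test". It adds: "A two-sided test and a significance level of α = 0.05 will be used".

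Objectives defines the primary endpoint as a count that can repeat within a patient: "The endpoints for this objective include all cardiac and device-related clinic visits". Design randomises patients one to one.

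Sample size justification takes its planning rate from one pooled figure: "Overall, 220 episodes occurred over 98 person-years (2.2 per person-year"). The source is "a population of 160 CRT-D patients followed up for 224 ± 130 days (data on file"). That rate becomes the control rate ("the incidence density used as a null hypothesis was 2.2 per person-year"), and for the effect "this rate is expected to decrease by 10% in the study arm". The section gives no between-patient variance, and the article nowhere mentions correlation of events within a patient.

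**The concern.** A comparison of two pooled incidence rates treats each visit as an independent piece of information. Its variance is right only if all patients share one underlying rate and one visit does not make another more likely. In a heart failure population with ICD and CRT-D devices this is a strong assumption. The article itself stratifies randomisation by time since implantation because it expects clinical stability to differ.

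If some patients are more prone to visits than others, the arm totals vary more than Poisson totals do. The test then uses too small a variance and its p-values are too small. This would affect the primary comparison and every secondary rate tested in the same way. The article names this test, so the point is about a stated choice and not about detail left to an unseen analysis plan.

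**Working it through.** **Inputs from the article.** 100 patients per arm, 16 months (1.333 years) of follow-up, 20% dropout spread uniformly, control rate 2.2 per person-year, rate ratio 0.90, two-sided α = 0.05.

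**Inputs assumed.** Patient rates follow a gamma distribution with mean 1 and variance k (coefficient of variation √k), so visit counts have variance mean + k × mean². The article gives no k; the range used is 0 to 2. A visit rate of 0.5 per person-year is a second assumption, explained in step 3.

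**Step 1: the plan's own figures.**
- Rate: 220/98 = 2.24 per person-year. Person-years: 160 × 224/365.25 = 98.1. Both agree with the article.
- Exposure per arm: 100 × 1.333 × (0.8 + 0.2 × 0.5) = 120 person-years. Expected events: 120 × 2.2 = 264 and 264 × 0.90 = 237.6.
- Power with no dispersion: Φ(|ln 0.90| / √(1/264 + 1/237.6) − 1.96) = Φ(0.1054/0.0894 − 1.96) = Φ(−0.78) = about 22%.
- The stated 99.8% does not reproduce, even under the independence that the test assumes. That is a separate error and owes nothing to clustering.

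**Step 2: type I error at the planning rate.**
- Mean exposure per patient: E[T] = 1.333 × 0.9 = 1.2. E[T²] = 1.333² × (0.8 + 0.2/3) = 1.541. Ratio E[T²]/E[T] = 1.284.
- Variance inflation: φ = 1 + k × rate × 1.284. At 2.2 this is 1 + 2.825k.
- Actual type I error: 2 × (1 − Φ(1.96/√φ)).

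| k | φ at 2.2 | type I error | φ at 0.5 | type I error |
|---|---|---|---|---|
| 0 | 1.00 | 5.0% | 1.00 | 5.0% |
| 0.1 | 1.28 | 8% | 1.06 | 6% |
| 0.25 | 1.71 | 13% | 1.16 | 7% |
| 0.5 | 2.41 | 21% | 1.32 | 9% |
| 1 | 3.82 | 32% | 1.64 | 13% |
| 2 | 6.65 | 45% | 2.28 | 19% |

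Type I error reaches 10% when φ is about 1.42. That is k = 0.42/2.825 = 0.15 at 2.2 per person-year, and k = 0.42/0.642 = 0.65 at 0.5.

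Gamma-Poisson simulation of the same design agrees with the table to about one percentage point. A continuity correction, on which the article is silent, takes off up to about two points; at 0.5 per person-year with k = 0.1 that is enough to offset the inflation. A patient-level robust variance held type I error at 5% to 6% throughout.

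**Step 3: why a second rate is needed.** The 220 planning events are device episodes: 140 impedance alerts, 34 + 6 atrial arrhythmia episodes and 40 shocks. The endpoint is unplanned visits. Not every episode leads to a visit, and symptoms cause visits without an episode, so the visit rate is unknown. The right-hand columns show how far the inflation shrinks if visits are rarer.

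**Step 4: power at rate ratio 0.90 with a valid variance.**
- Var(log rate ratio) = 1/264 + 1/237.6 + 2k × 1.541/(100 × 1.2²) = 0.0080 + 0.0214k.
- Power: about 22% (k = 0), 15% (0.25), 12% (0.5), 9% (1) and 7% (2). Simulation is within about two points.

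**The case against.** The strongest reply is that the documents do not show the size of the problem. That stands. A reader might infer that type I error is certainly well above 5%. It is exactly 5% with no dispersion, about 8% at k = 0.1 at the planning rate, and lower still if visits are rarer than device episodes. Only the conditional statement is supported.

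Three further inferences are tempting and do not hold:
- **A few unstable patients will supply most visits.** The Device programming text lets clinicians turn off the impedance alert "when recurrent inappropriate detections of fluid accumulation are documented". That concerns alerts, not visits, and switching the alert off would itself limit repeat visits. It does not establish how visits are distributed.
- **Confidence intervals for the effect are too narrow.** The article specifies no interval for the treatment effect; the only interval shown is around the simulated power.
- **Clustering explains the gap between 99.8% and the real power.** Nearly all of that gap exists with no clustering at all. Clustering accounts only for the further fall from about 22% to between 15% and 7%.

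It may also be said that an analysis plan could deal with clustering. It could, but only by overriding the test named here for the primary and secondary hypotheses. A plan that follows the article inherits the problem.

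**Conclusion.** The point holds in conditional form. The article commits to a test whose 5% error rate is valid only if all patients share one rate and visits are independent, for an endpoint that can recur within the randomised unit. Any material variation between patients raises type I error. For gamma variance from 0.1 to 2, it runs from about 8% to 45% at 2.2 events per person-year and from about 6% to 19% at 0.5 visits per person-year.

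The direction is secure. The size is not, because both the dispersion and the visit rate are assumptions. A common rate for every patient is nevertheless a hard assumption to defend here, and the article does not argue for it. Since the primary p-value depends on it and the remedy is cheap, the method should be changed before analysis.

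**What to change.** In Statistical methods, replace the named test by one primary model for all rate comparisons: Poisson regression of each patient's visit count on arm, with log person-time as offset and a patient-level robust (sandwich) variance. Give negative binomial regression as the sensitivity analysis. The two are not equivalent and can give different estimates and p-values, so the primary one must be fixed in advance. Drop the pooled-rate test as a basis for inference.

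In Sample size justification, restate the power at rate ratio 0.90 under a stated dispersion and a stated visit rate. The sponsor's file on 160 patients may inform the dispersion, with the caveat that it counts device episodes. Correct the 99.8% separately.

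The cost is revised analysis wording, a new power calculation and a little more analysis work. No new data or visits are needed. P-values will be less favourable if patients' rates differ, and almost nothing is lost if they do not.

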### Design

This is a one-to-one randomized, prospective study. The study has been approved by the Institutional Review Board of the 6 participating Italian centers.

Patients implanted with wireless-transmission-enabled Medtronic ICD or CRT-D will be randomized to "remote transmission on" (remote arm) or "remote transmission off" (standard arm) (Figure 1).

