**Figure 1 F1:**
[figure not shown]
**Trial design**. Enrollment and follow-up schedule.

Randomization will be stratified by center and by time from implantation (≤ 6 months and > 6 months) to minimize selection bias and preserve homogeneity between arms with regard to stability of clinical status.

In the remote arm, devices will be programmed to transmit over the CareLink Network. Devices in the standard arm will have all features available in their ICD/CRT-D, including the audible notification of alerts, but will not have access to the CareLink Network.

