Other trials have used a control arm blinded to device data [22], in order to test the clinical value of diagnostic features. By contrast, in the present study all alerts will be turned on for audible notification in the standard arm and the diagnostics will be open for in-office review. This will enable the benefits associated to remote notification and access to ICD data to be specifically assessed in addition to the diagnostic and alerting capabilities of modern ICD.

Another trial is currently investigating the CareLink system in pacemaker patients [23]. The present study on ICD/CRT-D patients, however, will focus on a sicker population with more complex devices. This is the setting in which remote monitoring is presumed to offer the greatest benefits.

In the hypothesis of a more stable clinical status of the patient and a reduced need to adjust ICD parameters 6 months after implantation [10], stratifying patient randomization on the basis of time since implantation will limit a potential bias.

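### Randomization is stratified by center and time from implantation, but the test named for the primary and secondary rates carries no stratification factor: a modest improvement that costs nothing

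*Protocol article*

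**What the plan says.** Protocol article, Methods/design, Design (text under Figure 1): "Randomization will be stratified by center and by time from implantation". Time from implantation has two levels, up to 6 months and over 6 months. The reasons given are selection bias and similarity of the arms in clinical stability. The Design section refers to "the 6 participating Italian centers", so there are up to 6 × 2 = 12 strata.

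Discussion, Rationale for design: patients are expected to be clinically more stable, and to need less device adjustment, 6 months after implantation. Hence "stratifying patient randomization on the basis of time since implantation will limit a potential bias".

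Statistical methods: "The primary and secondary hypotheses will be tested by using the Comparison of Incidence Rates (Large Sample) Test". The section adds "A two-sided test and a significance level of α = 0.05 will be used". It mentions no stratum, covariate or model.

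**The concern.** An analysis should normally respect the restrictions placed on the randomization. Here the plan regards two factors as important enough to randomize within, and it expects one of them to be related to clinical stability. The only test it names is a large-sample comparison of two incidence rates, which as named has no place for either factor.

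Two things could be at stake. First, stratified allocation keeps between-stratum differences largely out of the arm difference. An analysis that estimates its variance between patients and ignores the strata still counts those differences as noise, so it is conservative. Second, balance at randomization is balance in patients, not in person-time. If dropout later unbalances person-time within strata, an unstratified rate comparison does not correct for it.

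**Working it through.** **1. Inputs and the plan's own figure.** From the article: 100 patients per arm, 16 months, 20% dropout uniform over follow-up, 2.2 episodes per person-year, rate ratio 0.90, two-sided α = 0.05.

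- Person-years per arm = 100 × (0.8 + 0.2 × 0.5) × 16/12 = 120.
- Expected events: 120 × 2.2 = 264 and 264 × 0.90 = 237.6.
- SE of the log rate ratio = √(1/264 + 1/237.6) = 0.089.
- Power = Φ(0.1054/0.0894 − 1.96) = Φ(−0.78) ≈ 22%.

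The stated 99.8% (Sample size justification) does not reproduce. That is a separate matter. It is relevant here only because stratifying does not change it.

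**2. The named test's own variance.** The SE above contains event totals only, so between-stratum variation does not enter it. A simulation of 12 strata with assumed blocks of 4, dropout unrelated to arm and no further patient heterogeneity (3,000 runs per cell) gave, at rate ratio 0.90:

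| Assumed SD of stratum log rates | Unstratified power | Stratified power |
|---|---|---|
| 0 | 22.8% | 22.4% |
| 0.3 | 21.2% | 20.3% |
| 0.5 | 22.6% | 21.6% |

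Simulation error is √(0.22 × 0.78/3000) ≈ 0.8 points, so there is no gain. At rate ratio 0.75, with patients also varying in rate, rejection was 75.3% both ways. That figure is not usable power, because the event-count variance ignores such variation. With an assumed gamma variance of 1 between patients, type I error was about 31% to 36% for both tests.

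**3. A patient-level variance.** Same design inputs. Assumed, because the article does not give them: center log-rate SD, rate ratio between implantation groups, within-stratum gamma dispersion 0.5, blocks of 4. The comparison is a pooled log rate ratio with patient-level variance against Poisson regression with center and implantation terms and a sandwich variance.

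| Center SD; implantation rate ratio | SE pooled | SE stratified | Reduction | Power at 0.75, pooled to stratified |
|---|---|---|---|---|
| 0.2; 1.25 | 0.140 | 0.137 | 1 − 0.137/0.140 = 2% | about 51% to 53% |
| 0.3; 1.5 | 0.147 | 0.138 | 1 − 0.138/0.147 = 6% | about 48% to 53% |
| 0.5; 1.5 | 0.160 | 0.144 | 1 − 0.144/0.160 = 10% | about 41% to 50% |

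Part of the gain comes from a slightly liberal plain sandwich variance: type I error was 5.4% to 5.9% stratified against 4.0% to 5.0% pooled. If strata do not differ in rate, the gain is about zero.

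**4. At the plan's own effect.** With these SEs and |ln 0.90| = 0.1054, two-sided power is Φ(0.1054/SE − 1.96) + Φ(−0.1054/SE − 1.96). It moves from 11.7% to 12.0% in the mildest case (SE 0.140 to 0.137) and from 10.1% to 11.3% in the strongest (0.160 to 0.144).

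**5. Dropout.** Distortion requires rates that differ between strata and dropout that differs by both arm and stratum. Under an assumed crossed pattern of 30% against 10%, with event-count variance and stratum SD 0.3 and 0.5, unstratified type I error was 6.4% and 8.1%, against 5.6% and 5.1% stratified. With dropout unrelated to arm, the unstratified test already ran at 5.1% and 6.3%, so the added error is about 1 to 2 points. Power at 0.90 was 15.2% and 11.7% unstratified against 21.5% and 21.2% stratified. The direction of that loss follows from the direction assumed for the crossing.

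**The case against.** The strongest reply is that the harm does not attach to the test actually named. A reader might infer that the plan loses precision built into its design and that its confidence interval is too wide. The documents do not support this. The named test takes its variance from event counts, with an SE of about 0.09, and stratifying leaves its power unchanged. If visits cluster within patients, that interval is too narrow rather than too wide: the stratified patient-level SEs above are 0.137 to 0.144. Nor does the article state a precision goal; it gives bias and comparability of the arms as the reasons for stratifying. This part of the reply stands.

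A reader might also infer that dropout will bias the result. The Sample size justification assumes dropout uniform over follow-up and states no difference by arm or stratum, so the dropout figures above rest wholly on an assumed pattern. The trial is unblinded and the arms have different visit schedules, which makes a difference by arm conceivable, but nothing in the text establishes one.

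Clinics may restrict alert notification to business hours (Management strategies), but this is weak support for stratifying. CareLink alerts exist in the remote arm only, so such a choice would mainly change the treatment effect by center, which center main effects do not remove.

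Finally, this is a journal article, and the analysis plan, not shown, may stratify the comparison. The article neither calls the rates crude nor rules out a stratified form. That is fair, and it limits the point. But the article does more than stay silent: it fixes a specific test for the primary and secondary hypotheses, and that test as named omits the randomization factors.

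**Conclusion.** The mismatch between randomization and analysis is in the text and holds. Its size is modest. Under the event-count variance of the named test, the effect on power is about zero. Under a patient-level variance, stratifying reduces the SE by about 2% to 10% and adds about 2 to 9 points of power at a rate ratio of 0.75. At the plan's own 0.90 it adds about 1 point or less. These gains rest on assumed stratum differences, dispersion and block size, and they vanish if strata do not differ. Protection against person-time imbalance is a further benefit only if dropout differs by both arm and stratum. This is a free improvement, not a flaw that undermines the trial.

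**What to change.** In Statistical methods, replace the two-rate test with a negative binomial or Poisson rate model. It should have a log person-time offset, terms for arm, center (6 levels) and implantation group (2 levels), and a patient-level robust variance with a small-sample correction. Use main effects rather than 12 separate cells, so that sparse strata do not destabilise the fit. Report the stratified rate ratio with its 95% confidence interval for the primary and secondary rates. If the analysis plan already stratifies, saying so in this section is enough.

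The cost is wording only. Both factors are known at randomization, and no new data, patients or procedures are needed. Two expectations should be set. The change does not repair the stated 99.8% power. And if visits cluster within patients, the new interval will be wider than the named test's: at the assumed dispersion of 0.5, 0.137/0.09 to 0.144/0.09, or about 1.5 to 1.6 times as wide on the log scale.
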